### Sample Size Calculation

Previous studies show that the average number of caries lesions in Dutch children at the age of 5 years is 4.5 (SD 4.5) [12]. This information was used for study size estimation using G*power 3 [34]. This showed that the intervention group needed at least 149 participants to demonstrate a reduction in cumulative caries incidence of at least 30% with a statistically significant Mann-Whitney *U* test allowing for statistical power (1-β) of .8 and a 2-sided α of .05 as a threshold for statistical significance. With an anticipated 30% loss to follow up, the aim was to include at least 200 participants per group.

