**Secondary outcomes**					
	Clinical assessment of average number of decayed, missing, and filled surfaces and teeth with Merged International Caries Detection and Assessment System			✓	✓
	Clinical assessment of person time at risk for first cavity with Merged International Caries Detection and Assessment System and incidence density			✓	✓
	Clinical assessment of consequences of untreated dental caries with the PUFA (visible pulpal involvement, ulceration caused by dislocated tooth fragments, fistula, and abscess) index			✓	✓
	Clinical assessment of presence of dental plaque with Simplified Oral Hygiene Index, 6-surface method [41]			✓	✓
	Online questionnaire assessment of oral health behavior with self-developed items		✓	✓	✓
	Online questionnaire assessment of psychosocial constructs of the Health Action Process Approach items (action self-efficacy, risk perception, outcome expectancies, intention, action planning, coping planning, and action control), adapted from Gholami and Schwarzer (2014) [42]		✓	✓	✓
	Online questionnaire assessment of oral health–related quality of life with the Early Childhood Oral Health Related Quality of Life [43] scale			✓	✓
	Online questionnaire assessment of child cooperativeness at oral examinations with the Frankl behavior scale [44]			✓	✓

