### Secondary Outcomes

The average dmfs/dmft number and the caries incidence density (person-time at risk to the first cavity) will be calculated from the merged ICDAS scores. Consequences of untreated dental caries will be measured using the PUFA (visible pulpal involvement, ulceration caused by dislocated tooth fragments, fistula, and abscess) Index [46]. The presence of dental plaque will be determined with the 6-surface method of the Simplified Oral Hygiene Index [41]. Child cooperativeness during the outcome assessments will be documented by clinical assessors using the modified Frankl behavior scale [44].

Behavioral change over time will be assessed based on self-reported oral health behavior and psychosocial constructs from the HAPA, measured with online questionnaires at baseline, age 24 months, and age 48 months. The early childhood oral health–related quality of life will be measured using the Early Childhood Oral Health Impact Scale [43].

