### Demographics and Patient Characteristics

The demographic characteristics include the children’s age, sex, family composition, mother’s highest educational attainment according to the International Standard Classification of Education [47], and health literacy measured with the 16-item European Health Literacy Survey Questionnaire (HLS-EU-Q16) [48].

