### Design of Data Analyses

All analyses of the effectiveness of the TOHI will make use of the intention-to-treat principle. To prevent biased principal data analysis, concealment will be maintained during data analysis. The blinding of the study comparison will be broken only after the completion of data analysis for the evaluation of outcomes for children at the age of 48 months. After data cleaning and prior to data analysis, the amount and patterns of missing data will be explored. Sensitivity analysis will be used to explore the impact of missing data. The 3 following scenarios will be assumed: stability over time (last value carried forward or backwards to replace missing value), best case (largest positive change score observed to replace missing value), and worst case (largest negative change score observed to replace missing value).

The intervention effects for the cumulative caries incidence at 48 months and the average dmfs/dmft will be compared as the risk difference (additive scale), numbers needed to treat, and the relative risk (multiplicative scale), all with the 95% CI. Effects for subgroups (ie, WBC, education level of the mother, and health literacy) will be evaluated with interaction terms in a multivariate regression analysis. To determine incidence density and person-time at risk, the median and mean between-group differences in caries incidence (or the person-time to first caries lesion) will be based on a Kaplan-Meier analysis and incidence differences and ratios. In addition, when applicable, Cox proportional hazard regression analysis will be applied to explore relations with independent variables. Between-group differences at the age of 24 months will be assessed for the secondary outcomes, notably changes in the behavioral determinants (defined according to the HAPA), plaque, and self-reported oral health behavior, using linear regression analysis. Results from all analyses will be presented with the 95% CI. For all analyses, the SEP stratum will be used as the primary covariable, while sociodemographic characteristics for which a baseline difference is observed will be used as secondary covariables. Such postrandomization differences between groups will be explored using descriptive statistics. A difference of 20% for discrete variables, a full standard deviation (pooled) for normally distributed data, and a quartile for nonnormally distributed data will be used as thresholds for similarity.

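### The 24-month comparison of changes in HAPA determinants has a covariate rule that leaves out the baseline score, at a cost in precision for secondary outcomes

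*Protocol article*

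**What the plan says.** The analysis of behavioural outcomes at 24 months is described in one sentence of the protocol article, under Design of Data Analyses. Group differences in the secondary outcomes are to be assessed, "notably changes in the behavioral determinants (defined according to the HAPA), plaque, and self-reported oral health behavior, using linear regression analysis". The best-case and worst-case missing-data scenarios in that section are also framed as change scores.

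The covariate rule follows: "For all analyses, the SEP stratum will be used as the primary covariable, while sociodemographic characteristics for which a baseline difference is observed" enter as secondary covariables. The thresholds for such a difference are then given: "A difference of 20% for discrete variables, a full standard deviation (pooled) for normally distributed data", and a quartile for nonnormal data.

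Three other places matter:

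- Secondary Outcomes says that self-reported behaviour and the HAPA constructs are "measured with online questionnaires at baseline, age 24 months, and age 48 months". Table 2 agrees: the row "Online questionnaire assessment of psychosocial constructs of the Health Action Process Approach items" and the behaviour row are ticked at T0, T1 and T2.
- Demographics and Patient Characteristics begins: "The demographic characteristics include the children’s age, sex, family composition, mother’s highest educational attainment". Health literacy is added, and no HAPA or behaviour score appears in the list.
- The Table 2 row "Clinical assessment of presence of dental plaque with Simplified Oral Hygiene Index, 6-surface method" is ticked at T1 and T2 only.

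**The concern.** The plan names an outcome form (change), a model (linear regression) and a covariate set. The baseline value of the score being analysed is not in that set, and it is not a sociodemographic characteristic that the imbalance rule could bring in. It is usually among the best predictors of the later score, and the trial already collects it.

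Subtracting the baseline is not the same as adjusting for it. Subtraction fixes the baseline coefficient at 1, whereas regression estimates it. When the true slope is below 1, subtraction over-corrects. The estimate then carries extra noise, and an arm that happens to start higher looks worse on change through regression to the mean.

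The article lists the HAPA constructs and oral health behaviours as expected mediators and secondary outcomes, and the abstract announces their 24-month comparison. Avoidable imprecision there makes it harder to tell an intervention that failed to move the determinants from one whose effect was missed.

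**Working it through.** **The plan's own figure.** There is none for this analysis. The only sample size calculation concerns the primary caries outcome and does not bear on this point.

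**Inputs from the article.** Allocation is 1:1, with 402 dyads randomized (201 per arm) and at least 200 per arm planned with 30% loss. That leaves 200 × 0.70 = 140 per arm. The 30% is the overall loss allowance, so 24-month numbers may be higher. The variance ratios below do not depend on n.

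**Assumptions, because the documents give no figure.** The baseline-to-24-month correlation r is 0.3, 0.5 or 0.7. The SD is 1 at both times. Power is for a 0.3 SD effect at two-sided 0.05.

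**Step 1: could the imbalance rule bring the baseline score in?** Even if HAPA scores were read into the rule, the threshold for normal data is 1 pooled SD. The standard error of a baseline mean difference is √(2/201) = 0.10 SD, so the threshold is about 10 standard errors away. With 140 per arm it is √(2/140) = 0.12 SD, about 8 standard errors. Chance will not trigger it.

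**Step 2: precision.** Per-subject variance is 2(1 − r) for change and 1 − r² with baseline adjustment. The ratio is 2/(1 + r). The 95% CI half-width is 1.96 × √(2 × variance/140).

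| r | Variance, change | Variance, adjusted | Ratio | CI half-width (SD), change / adjusted | Power, change / adjusted |
|---|---|---|---|---|---|
| 0.3 | 1.40 | 0.91 | 1.54 | 0.277 / 0.223 | 56% / 75% |
| 0.5 | 1.00 | 0.75 | 1.33 | 0.234 / 0.203 | 71% / 83% |
| 0.7 | 0.60 | 0.51 | 1.18 | 0.181 / 0.167 | 90% / 94% |

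Put as sample size, the adjusted analysis needs 140 × (1 + r)/2 = 91, 105 or 119 per arm to match the change score with 140. Below r = 0.5 the change variance exceeds 1, so the change score is then less precise than comparing 24-month values and ignoring baseline.

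**Step 3: conditional shift.** Given a chance baseline difference D, the expected change-score estimate moves by (r − 1) × D. For D = 0.2 SD (about 1.7 standard errors with 140 per arm) the shift is −0.14, −0.10 or −0.06 SD at r = 0.3, 0.5 or 0.7. The adjusted estimate does not move in expectation.

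**Step 4: simulation check.** In 10,000 simulated trials per correlation with 140 per arm, the variance ratios were 1.54, 1.34 and 1.17. The slopes of the estimate on baseline imbalance were −0.70, −0.49 and −0.30 for change, and 0.00, 0.01 and 0.00 with adjustment.

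**Step 5: unequal SDs.** With baseline SD s1 and follow-up SD s2, the variances are s1² + s2² − 2r·s1·s2 (change) and s2²(1 − r²) (adjusted). They coincide when s1 = r·s2.

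- For s1 = 0.8, s2 = 1, r = 0.7: 0.64 + 1 − 1.12 = 0.52 against 0.51, a gap of only 2%.
- For s1 = 1.25, s2 = 1, r = 0.7: 1.5625 + 1 − 1.75 = 0.81 against 0.51, a ratio of 1.59.

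**The case against.** The strongest reply is that the article never says that baseline is excluded. It ranks primary and secondary covariables, gives no model equation, and is a condensed text whose SAP is not shown. A regression of the 24-month score on arm and baseline would not contradict the words linear regression analysis. It is right that the omission is inferred from the covariate list, and a reader should not infer that the plan expressly rules out baseline adjustment. But the rule is stated for all analyses, and an SAP that followed it literally would leave the baseline score out. This is therefore a stated rule to improve and not merely missing detail.

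Other points on that side also stand:

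- A change score does use the baseline, by subtraction, and is unbiased on average under randomization.
- It is not true that change is less precise whenever the correlation is below 1. That needs equal SDs (step 5).
- A low correlation might be argued from the children's age at baseline (6 to 12 months). The HAPA constructs are parental, and no figure in the documents bears on r.
- The list in the analysis sentence can be parsed so that changes refers only to the HAPA determinants, with plaque and behaviour as separate items. On that reading plaque is already compared as a level, which fits Table 2. The text does not establish that an impossible plaque change is planned.

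**Conclusion.** The point holds as a worthwhile improvement that costs nothing, for secondary outcomes only. As written, the 24-month analysis of changes in HAPA determinants, and on one reading of self-reported behaviour, does not list the baseline score among its covariates although it is collected.

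The consequences are a loss of precision and a conditional shift under chance imbalance. With equal SDs, the variance is 1.54, 1.33 or 1.18 times larger at r = 0.3, 0.5 or 0.7. These figures illustrate the size over an assumed range and do not estimate it for this trial. With unequal SDs the gap can nearly vanish or grow. In large samples, baseline adjustment is never the less precise of the two.

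A reader might infer that the behavioural results will be biased, or that the primary caries endpoint is affected. The documents support neither. The response scales of the self-developed behaviour items are not given, so nothing here shows that linear regression is the wrong model type for them. For plaque, the only defect is ambiguous wording.

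**What to change.** State that, for each HAPA construct and behaviour score, the 24-month regression (and any 48-month regression) includes the baseline value of that score as a prespecified covariate, whatever imbalance is observed. Arm and both randomization strata, WBC and maternal education, should be in the same model. The covariate rule for all analyses should carry this as an explicit addition.

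Change can still be the reported quantity. With the baseline score in the model, regressing the change or the 24-month value gives the same arm estimate and standard error.

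Reword the list in the analysis sentence so that it is clear which outcomes are compared as changes, and say that plaque is compared as a 24-month level.

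The cost is wording only. The baseline scores are already collected, and a change score needs them too, so no participant is lost by adjusting. The amendment should be dated before unblinded data are examined.

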### Intervention Randomization

With a 1:1 ratio, participating parent-child dyads were individually allocated to the intervention or control group. This allocation of the TOHI as an add-on to usual care was stratified for each WBC (9 in total) and educational level of the mother (classed as low, medium, or high) as an indicator of SEP. A computerized random sequence generator [35] with a block size of 4 to ensure equally filled strata in each group was used to allocate the intervention status to predefined unique ID numbers. Accordingly, an intervention allocation file was prepared, including intervention codes with blocked series of ranked unique participant IDs for the strata.

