## Results

The first parent-child dyads were enrolled in June 2017, and recruitment finished in June 2019. In total, 402 dyads have been randomized. Interventions and data collection for all of these dyads will be completed by the end of 2022. Therefore, final results are expected in the first half of 2023.

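### The adjustment rule leaves out clinic, a randomisation stratum, and picks further covariates by observed imbalance rather than prognostic value; the cost is modest precision, not bias

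*Protocol article*

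**What the plan says.** The Intervention Randomization section describes individual allocation "With a 1:1 ratio", "stratified for each WBC (9 in total) and educational level of the mother (classed as low, medium, or high) as an indicator of SEP", "with a block size of 4". That makes 9 × 3 = 27 strata.

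The Design of Data Analyses section then sets the adjustment rule:

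- Fixed covariate: "For all analyses, the SEP stratum will be used as the primary covariable".
- Further covariates: "sociodemographic characteristics for which a baseline difference is observed will be used as secondary covariables".
- What counts as a baseline difference: "A difference of 20% for discrete variables, a full standard deviation (pooled) for normally distributed data", and a quartile for data that are not normally distributed. Whether 20% is absolute or relative is not said.

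The same section names clinic, maternal education and health literacy as subgroup factors, to be examined through interaction terms. That is the only analysis role given to clinic.

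**The concern.** Two features of the rule do not fit the design.

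First, clinic was balanced by design but is absent from the model for the main effect. The SEP stratum cannot be read as including clinic, because the randomisation section makes maternal education the indicator of SEP. When a stratification factor predicts outcome and is left out, the usual SE ignores the balance already bought, so intervals are a little wide and the test a little conservative.

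Second, under concealed randomisation, baseline differences between arms are due to chance. Their size says nothing about whether a variable predicts caries, and prediction is what makes adjustment worthwhile. A rule keyed to imbalance can pass over a strong predictor and admit an irrelevant one.

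At stake is precision for the primary outcome, and a covariate set that two analysts applying the same sentence would both arrive at.

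**Working it through.** The article gives no figure for the adjustment rule, so there is none to reproduce.

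**Inputs from the article.** "In total, 402 dyads have been randomized" (Results), so about 201 per arm. Anticipated loss is 30% (Sample Size Calculation), leaving 402 × 0.70 ≈ 281 children, about 140 per arm. Dentin caries affects about one-third of Dutch five-year-olds (Introduction); this stands in for control risk at 48 months and is an assumption.

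**Assumed.** Between-clinic variation in caries risk, which the article does not give.

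**1. How often the cut-offs trigger under valid randomisation, 201 per arm**

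- *One pooled SD.* SE of a standardised mean difference = √(2/201) = 0.0998. So 1 SD = 1/0.0998 = 10.0 SE; two-sided chance about 1e-23.
- *A quartile*, read as median to upper quartile (0.674 SD for normal data). SE of the difference in medians = √(π/2) × 0.0998 = 0.125. So 0.674/0.125 = 5.4 SE; chance about 7e-8.
- *20% as percentage points, 50% prevalence.* SE = √(2 × 0.25/201) = 0.0499. So 0.20/0.0499 = 4.0 SE; chance about 6e-5 (exact binomial 5e-5). At 30% and 10% prevalence the distance is 4.4 and 6.7 SE.
- *20% as relative, 10% prevalence.* The cut-off is 0.02 and SE = √(2 × 0.09/201) = 0.0299. So 0.02/0.0299 = 0.67 SE; chance about 0.50 (exact 0.52).

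Exact binomial chances for the 20% rule:

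| Prevalence | 20 points, 201/arm | 20 points, 140/arm | Relative 20%, 201/arm | Relative 20%, 140/arm |
|---|---|---|---|---|
| 50% | 5e-5 | 1e-3 | 0.05 | 0.10 |
| 30% | 1e-5 | 3e-4 | 0.19 | 0.28 |
| 10% | 4e-11 | 7e-8 | 0.52 | 0.59 |

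**2. Cost of leaving clinic out, by formula**

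With overall risk 1/3, outcome variance is 1/3 × 2/3 = 0.222. For between-clinic SD s, the SE ratio (clinic omitted to clinic included) is 1/√(1 − s²/0.222):

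- s = 0.10: 1/√(1 − 0.0100/0.222) = 1.023, about 2%.
- s = 0.15: 1/√(1 − 0.0225/0.222) = 1.055, about 5%.

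This counts all clinic variation as unexplained by education, so it leans high.

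**3. Cost by simulation**

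The design was simulated with 402 dyads, 27 strata, blocks of 4, 30% random loss, control risk about 1/3 and a linear risk-difference model with robust SE. There were 4,000 runs under the null and 3,000 with a 30% relative reduction.

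| Assumed clinic SD (logit) | Type I: education only | Type I: education + clinic | Power: education only | Power: education + clinic | Mean null SE: education only | Mean null SE: education + clinic |
|---|---|---|---|---|---|---|
| 0 | 0.050 | 0.049 | 0.47 | 0.47 | 0.0556 | 0.0558 |
| 0.5 | 0.043 | 0.049 | 0.50 | 0.51 | 0.0558 | 0.0548 |
| 1.0 | 0.040 | 0.053 | 0.51 | 0.56 | 0.0561 | 0.0521 |

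On the risk scale, a logit SD of 0.5 is roughly 0.5 × 0.222 = 11 points and 1.0 roughly 22 points. The 5-point power loss therefore belongs to clinic variation larger than in step 2. At about 11 points the loss is about 1 point of power.

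**The case against.** The strongest reply is that little harm follows, and much of it stands.

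- *Clinic.* Omission leaves the estimate unbiased and does not inflate type I error. The loss depends on a between-clinic SD the article never gives. It may be small, since education is already in the model and the clinics were chosen to serve mainly lower-SEP or low-to-middle-SEP neighbourhoods. A reader might infer that the trial's result is invalid, or that it cannot afford the loss. Neither follows from the article.
- *An open model.* A reader might infer that the primary model stays open until the data are seen. On the absolute reading the cut-offs almost never trigger, so the model is in effect treatment plus education. Only the relative reading makes chance selection common, and then only for discrete characteristics, mainly uncommon categories; the article gives no prevalences. The rule uses baseline data with stated cut-offs, and the article keeps the comparison blinded until the 48-month analysis is complete, so it cannot be tuned to the outcome.
- *Health literacy.* A reader might infer that it goes unused. It is a subgroup factor and is listed among the demographic characteristics, so it could become a secondary covariable. It is only not a fixed covariate for the main effect.

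What the reply does not remove: a subgroup interaction is no substitute for adjusting the main effect, and imbalance is a poor selection criterion under either reading of 20%. Nor is this detail left to an analysis plan, since the article states the rule, its scope and its cut-offs.

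**Conclusion.** The point holds as a recommendation to improve a stated rule, not as a threat to validity. One of the two randomisation strata is missing from the main-effect model. The price ranges from nothing, if clinics do not differ, to an SE about 2% to 5% larger at an assumed clinic SD of 10 to 15 percentage points. In simulation the power loss is 0 to about 5 points, the upper end needing clinic variation above that range. These sizes also rest on an assumed control risk of about one-third.

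The imbalance rule does little useful work. With 20% read as percentage points it practically never acts. Read as relative, it acts by chance, in about 5% of trials for a 50%-prevalence characteristic and about half for a 10%-prevalence one. In neither case does it select on prognosis.

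**What to change.** Before the comparison is unblinded:

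1. State that all effectiveness analyses adjust for both randomisation strata, clinic and maternal education.
2. Replace the imbalance rule and its cut-offs with a short covariate list fixed in advance on prognostic grounds from baseline data already collected, for example health literacy. Adjust for it whatever imbalance is seen.
3. Keep the baseline comparison of the arms descriptive.

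Marginal standardisation is one suitable way to report the adjusted risk difference and relative risk; it is an option, not a required correction.

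The cost is wording, with no new data. Clinic uses 9 − 1 = 8 degrees of freedom among about 281 analysed children. If clinics do not differ, the SE rises negligibly (0.0556 to 0.0558 in the simulation, about 0.4%).
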